# A person-centred care transition support for people with stroke/TIA: A study protocol for effect and process evaluation using a non-randomised controlled design

**DOI:** 10.1371/journal.pone.0299800

**Published:** 2024-03-14

## Abstract

**Introduction:**

Care transitions following a stroke call for integrated care approaches to reduce death and disability. The proposed research described in this study protocol aims to evaluate the effectiveness of a person-centred multicomponent care transition support and the process in terms of contextual moderators, implementation aspects and mechanisms of impact.

**Methods:**

A non-randomized controlled trial design will be used. The intervention includes person-centred dialogue intended to permeate all patient-provider communication, various pedagogical modes of information, a person-centred care and rehabilitation plan, and a bridging e-meeting to prepare patients for homecoming. Patients with stroke or TIA who are to be discharged from the participating hospitals to home and referred to a neurorehabilitation team for continued rehabilitation will be included. Follow-ups will be conducted at one week, 3 months and 12 months. Data will be collected on the primary outcome of perceived quality of the care transition, and on the secondary outcomes of health literacy, medication adherence, and perceived person-centeredness. Data for process evaluation will be collected through semi-structured interviews, focus groups, participatory observations, and the Normalisation Measure Development Questionnaire.

**Discussion:**

The study will provide insights on implementation, mechanisms of impact, contextual moderators, and effectiveness of a care transition support, targeting a poorly functioning part of the care trajectory for people with stroke and TIA.

**Clinical trial registration:**

ClinicalTrials.gov Identifier: NCT05646589.

## Introduction

Stroke is a life-threatening condition that needs acute treatment [1]. Strong evidence has shown that stroke care should initially be supplied at hospital stroke units [2]. Sweden is considered to have efficient medical acute stroke care [3], with short hospitalizations and follow-up in primary or secondary care. Thus, the stroke chain of care always implies a transition from inpatient care to outpatient care organized by primary or secondary care, i.e., a shift in responsibility from one healthcare setting to another.

For the patients and their significant others, an uncoordinated care transition may be a burden, especially when they lack experience in navigating the healthcare system [1]. Cognitive impairments, post-stroke fatigue and depression [4], and the sudden onset of stroke or transient ischemic attack (TIA), often render patients and their significant others unprepared for the care transition to their home [5, 6]. In addition, the short hospital stay leaves little time to participate in transition planning [7, 8], leading to a sense of being abandoned to a new and complex life situation after discharge [7]. The Swedish Health and Medical Service Act states that care providers are responsible for coordinating care. Nevertheless, a great responsibility falls on the patient and significant others to coordinate the care transition [9] and few arrangements support the ability of the patients to participate in their care or self-management after discharge [10, 11].

Studies have shown that there are gaps between the information provided by healthcare professionals and the information that patients can understand and apply. Although 90% of recently discharged older people stated that they had understood the discharge information, 40% could not recall their diagnosis and 23% could not recall their planned follow-up [12]. Another study identified that 62% of recently discharged older persons could not recall their new medications [13]. Our pre-studies have shown that present care transitions are not tailored to support the patient’s understanding of the health information that is needed for self-management after hospital discharge [7, 8]. Self-management of secondary stroke prevention, for example medications, is crucial, as recurrent strokes account for 21% of all strokes [14]. Hence, persons who do not understand information supplied at the time of hospital discharge are at risk of another stroke, since they may not adhere to the prescribed secondary stroke prevention treatment. Consequently, at each patient-provider meeting at the hospital, it is critical to ensure that patients understand the health information supplied, to enable self-management of secondary prevention [15].

As part of Sweden’s national system for knowledge-driven management within healthcare, a national person-centred and cohesive care process for stroke and TIA has been developed. The cohesive care process aims to provide equal and effective care based on the best available knowledge. This emphasises the need to develop tailored communication modes, to meet the various information needs of persons with stroke and TIA [16]. From an equality perspective, it is crucial that all patients, regardless of communicative skills and cognitive capacity, not only receive but also understand and have knowledge and competence to use the health information.

The knowledge and competence that enables people “to access, understand, appraise and use information and services in ways that promote and maintain good health” has been defined by the World Health Organization (WHO) as health literacy [17]. WHO emphasizes that health literacy does not only depend on the individual’s ability, the capacity of healthcare organizations to provide services that support the patient’s knowledge and competence is equally important [17]. Low health literacy, which is common after stroke [18], is associated with reduced adherence to medical advice, greater healthcare utilization, and among older persons also an overall poorer health status and higher mortality [19]. Thus, it has been strongly suggested that to enhance self-management after stroke, healthcare services should be tailored to meet the varying levels of patient health literacy [20]. To improve patients’ self-management of secondary prevention, a recent systematic review concluded that “future research should focus on the development of more effective interventions, to translate secondary prevention recommendations into practice” [21]. Therefore, this study translates the intention of the Swedish Health and Medical Service Act, the recommendations of the Swedish person-centred and cohesive care process for stroke and TIA, and recommendations for secondary stroke prevention, into an adaptive person-centred multicomponent care transition intervention, co-designed to fit in practice and tailored to patient needs.

### The intervention

The intervention was developed according to the Medical Research Council framework of complex interventions [22], which calls for phased and iterative approaches in the design and evaluation. Hence, the intervention has been developed by identifying the evidence base for the care transition literature [23–26], understanding local needs and context through our pre-studies [7, 8, 27], and by conducting a co-design process [28] with patients, significant others, and healthcare professionals. The intervention has been tested in a feasibility study investigating fidelity, acceptability, and implementation aspects [29, 30]. Preliminary results show that the intervention is feasible from the perspective of healthcare professionals and patients, and that the proposed methods for evaluation are suitable for patients who recently had a stroke, as well as for their significant others [30]. The intervention has been developed considering both the patient perspective and that the intervention should be context-sensitive and feasible to adapt by the healthcare professionals in diverse organizational settings. Based on the work on building program theory for complex interventions that adapt to context by Mills et al., [31], we constructed a type 4 logic model, mapping the mechanisms, activities, moderators, and anticipated outcomes, which is presented in Fig 1 and described in the text below.

**Fig 1 pone.0299800.g001:**
[figure not shown]
A type 4 logic model, mapping the mechanisms, activities, moderators, and anticipated outcomes of the person-centred multicomponent care transition intervention.

The intervention targets how healthcare professionals can improve the quality of the care transition and support health literacy for self-management of secondary prevention for persons who are to be discharged from hospitals after stroke or TIA. The core intention of the intervention therefore aims to create a person-centred care transition where:

Staff understand what matters to the patient and tailor their efforts to the unique needs, values, preferences, and resources of the individual.Patients are active participants and co-creators in decisions about their care and rehabilitation (provided that is what they desire).Patients understand their health condition and what is happening to them.Patients understand the prescribed secondary prevention treatment and self-management.Patients understand what to expect after discharge in terms of follow-up and rehabilitation.A mutual understanding between patients and healthcare professionals is created.

### Intervention components

The intervention includes a set of components that will stimulate the fulfilment of the core intentions. The components include a person-centred dialogue intended to permeate all patient-health professional communication during the acute hospital stay and the continued rehabilitation in the home environment. The person-centred dialogue consists of three different parts [32, 33]: 1) The patient part focuses on the patient’s narrative of “What matters to the patient?” This involves the exploration of patient needs, values, preferences, resources and expectations by the healthcare professionals; 2) The healthcare professional part focuses on the provision and assurance of understanding of information based on the needs of the patient. The objective is to support the patient’s understanding of their health condition, including management of secondary prevention; and 3) The mutual part focuses on a summary and shared understanding of both the patient and professional perspective and mutual agreement on a plan forward. Teach Back-methodology [34, 35] is used in all three parts of the person-centred dialogue. The intervention also includes various pedagogical modes of information: informative recorded videos and written information leaflets with a presentation of the neurorehabilitation team; plans for follow-ups and rehabilitation after discharge; a structured discharge letter on secondary preventive medications, the health condition, and plans for follow-ups. The information is intended to be used at the discharge encounter. Further, a bridging e-meeting is offered to prepare patients for homecoming. The bridging e-meeting before discharge includes the patient, their significant other, healthcare professionals at the hospital and the neurorehabilitation teams in primary care.

### Intervention mechanisms and contextual moderators

As intervention mechanisms are "the interaction between program resources (components) and the ways that participants interpret and respond (or not) to them; an explanatory account of how and why programs give rise to outcomes; hidden, but still real shaped by and interconnected with context" [36], we can only hypothesize about potential mechanisms contributing to our intended outcomes. However, based on our pre-studies, co-design process, and feasibility study, we have gained insight about mechanisms as well as outer and inner context moderators that can shape intervention components and contribute to outcomes, illustrated in Fig 1.

Several potential contextual moderators might exert an influence in the outer and inner context, as suggested in Fig 1. These contextual moderators can both have a positive and negative influence on the implementation, program activities and mechanisms. The feasibility testing made it evident that the intervention is context-sensitive, and the embedding of the intervention varied between settings and healthcare professionals, indicating the need for non-linear evaluation methods.

The overall aim is to evaluate the co-designed adaptive multicomponent care transition intervention. We hypothesise that the person-centred multicomponent care transition will improve the patients’ perceived quality with care transitions, and knowledge and competence to use health information, i.e., health literacy, which in turn may reduce recurrent stroke/TIA and healthcare utilization during the first year after stroke, as well as alleviating caregiver burden for significant others.

Research questions (RQ):

Does a person-centred multicomponent care transition intervention have an effect on perceived quality with care transitions, health literacy, collected medications, medication adherence, perceived person-centeredness, functioning, recurrent stroke/TIA, healthcare utilization and caregiver burden?What are the experiences of the intervention components and the implementation process?How does the intervention get adapted and implemented in practice?What contextual moderators and mechanisms of the intervention can likely explain the potential effects of the intervention?

## Materials and methods

### Theory

#### Complexity theory

With the complexity of transitional care, we acknowledge that the intervention involves many adaptive aspects that need to be implemented in a dynamic and complex system. The intervention involves communication and interaction between several agents, i.e., patients with various needs, healthcare professionals and also between different professions in multiple settings—all with various knowledge and competences for communication. Such complexity, defined as a “dynamic and constantly emerging set of processes and objects that not only interact with each other, but come to be defined by those interactions” [37] calls for new approaches in relation to implementation and the evaluation of impact. Based on knowledge generated from our feasibility studies, these agents interact dynamically in a non-linear fashion, which contributes to an unpredictability in how the intervention is embedded and delivered in practice. The behaviours and interactions between these agents contribute to the emergence of the system and this is fundamental to how the intervention behaves [38]. As systems are embedded in a wider context of nested systems that relate to and interact with each other, it is of particular importance to consider the influence of the setting and context when implementing and evaluating interventions in healthcare. Further, as agents and systems co-evolve and self-organise to best fit with the context and the environment [39], the intervention is expected to be adapted differently by and between different agents and contexts. We therefore conclude that the complex, dynamic system of care transitions has outgrown the use of reductionist scientific methods. We must therefore apply methods with a complexity lens that best deals with uncertainty, unpredictability, and generative causality [40].

#### Normalization process theory

To be able to comprehend the uncertainty, dynamics and emergency that implementing an adaptable intervention in a complex system involves, we also need to consider the process of implementation. To facilitate implementation and understand how the healthcare professionals operationalize the intervention, we will use Normalization Process Theory (NPT) as a guide [41]. NPT is a theory of implementation that focuses on what people do, i.e., concentrates attention on the individual and collective behaviour of the implementation process. NPT will be used to understand the social organization of the implementation and how the intervention is embedded and sustained in everyday practice [42, 43]. NPT describes four generative mechanisms; coherence, cognitive participation, collective action and reflexive monitoring [41]. Coherence entails sense-making, i.e., actions to promote professionals’ understanding of how the new practice, the person-centred multicomponent intervention, differs from the usual practice. Cognitive participation entails building and sustaining a community of practice around the new intervention. Collective action is what people do to operationalize and embed the intervention in clinical practice. Reflexive monitoring is the appraisal of how the intervention is understood and assessed by the professionals operationalizing it, which involves evaluating the effects, determining the value of the intervention, and modifying the intervention if needed.

### Study design

We will apply a non-randomized controlled trial design, which is well suited for assessing the effectiveness of complex interventions and allows for a detailed process evaluation. Randomization at the patient level is not suitable, due to the risk of contamination. Further, the use of a non-randomized controlled trial design makes it possible to consider the roles of mechanisms, context, and the complexity of transitional care, during implementation and evaluation. We will use a research design with two intervention sites and two control sites, including multiple follow-ups over a period of one year [44] and, in two parallel phases, we will focus on evaluation of both effect and process. The SPIRIT Checklist was utilized to ensure high-quality reporting of this protocol, for detailed information see S1 Appendix.

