#### Setting

The intervention will be conducted in the Stockholm region at one acute stroke unit and one geriatric stroke ward and will involve the corresponding neurorehabilitation teams in primary care. Another acute stroke unit and geriatric stroke ward, with the corresponding neurorehabilitation teams in primary care, will serve as control sites. Patients at the control sites will receive standard care transitions. Based on our pre-studies, “standard care transitions” means that the care transition is initiated by an electronic referral from allied health professionals at the hospital to the receiving neurorehabilitation team. The referral notifies the neurorehabilitation team about the patient’s discharge. The teams are then obliged to contact the patient within 48 hours after hospital discharge. Further, a discharge meeting is held with the patient and responsible physicians. Patients receive a standard discharge letter and an informational leaflet about the neurorehabilitation team.

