#### Sample size

Results from our pre-studies show that participants had a mean of 62 points in the care transition measure and standard deviation of 21. Based on the estimation that satisfaction will be a mean of 72 in the person-centred multicomponent care transition, we will need to recruit 70 patients (80% power, p = 0.05, 2 sided). Allowing for 20% drop-out, we will need to recruit in total 84 patients per group, 168 patients in total.

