#### Analyses

Patients in the intervention group will be compared to the control group using intention-to-treat and per-protocol analysis. Regression models adjusting for covariates (e.g., age, gender, stroke severity, and other disease-related data) will be used for analyses of primary and secondary outcomes. Analyses will be performed and reported in accordance with the Consolidated Standards of Reporting Trials guidelines for non-randomized controlled trials [46].

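### The stated 80% power treats patients as independent although treatment is assigned by site, two versus two; it holds only if no between-site variance remains after adjustment

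*Protocol article*

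**What the plan says.** Under Study design: "We will use a research design with two intervention sites and two control sites". Under Setting, the intervention runs "at one acute stroke unit and one geriatric stroke ward", and for the comparison: "Another acute stroke unit and geriatric stroke ward, with the corresponding neurorehabilitation teams in primary care, will serve as control sites". Treatment therefore follows the site, and each arm holds one site of each type.

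Under Sample size, the inputs are that "participants had a mean of 62 points in the care transition measure and standard deviation of 21" and the expectation that "satisfaction will be a mean of 72 in the person-centred multicomponent care transition". The result is "we will need to recruit 70 patients (80% power, p = 0.05, 2 sided". The next sentence inflates this to 84 per group, so the 70 is per group. No ICC, design effect or site variance appears.

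Under Analyses (Phase 1): "Regression models adjusting for covariates (e.g., age, gender, stroke severity, and other disease-related data) will be used for analyses of primary and secondary outcomes". The covariates named are patient characteristics. No site term or clustering method is named, but the list is open.

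Under Intervention mechanisms and contextual moderators, the feasibility work is said to have shown that "the embedding of the intervention varied between settings and healthcare professionals". The Complexity theory section adds that the authors expect adaptation to differ between contexts.

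**The concern.** When whole sites are assigned, patients at one site share staff, routines and a receiving rehabilitation team. The primary outcome is the patient's rating of the care transition, which is what the site and its team deliver. If sites of the same type differ in mean CTM score for reasons other than the intervention, the contrast between arm averages carries that difference. A standard error based on independent patients reflects it too weakly.

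Two things are at stake. The stated power may be well above the real one. And a patient-level test, if used without allowance for site, could report a difference between hospitals as an intervention effect more often than 5% of the time.

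**Working it through.** **Inputs from the article.** Difference 72 − 62 = 10 points; SD 21; two-sided 5%; 80% power; 70 analysable per arm; two sites per arm.

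**Assumed, because the article does not give them.** The residual ICC, shown from 0 to 0.05, with total SD held at 21; and an equal split, m = 70/2 = 35 analysable patients per site.

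**Step 1: reproduce the plan's figure.** n per arm = 2 × (1.96 + 0.84)² × 21²/10² = 2 × 7.85 × 441/100 = 69.2, rounded up to 70. This matches exactly. It is the formula for independent patients, with a design effect of 1.

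**Step 2: allow for residual site variance.**
- Site SD = 21 × √ICC
- Design effect DE = 1 + (35 − 1) × ICC
- SE of the difference = 21 × √(2 × DE/70)
- Power = Φ(10/SE − 1.96), taking the ICC as known
- Type I error of a patient-level test that ignores site = 2 × (1 − Φ(1.96/√DE))
- Site-level t-test: noncentral t with 4 − 2 = 2 df, critical value 4.30, noncentrality 10/SE

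| ICC | Site SD (points) | DE | Effective n per arm | SE | Power | Type I error, site ignored | Power, site-level test (2 df) |
|---|---|---|---|---|---|---|---|
| 0 | 0 | 1.00 | 70 | 3.55 | 80% | 5% | 36% |
| 0.01 | 2.1 | 1.34 | 52 | 4.11 | 68% | 9% | 29% |
| 0.02 | 3.0 | 1.68 | 42 | 4.60 | 58% | 13% | 25% |
| 0.05 | 4.7 | 2.70 | 26 | 5.83 | 40% | 23% | 18% |

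For ICC 0.02, as an example: DE = 1 + 34 × 0.02 = 1.68; SE = 21 × √(3.36/70) = 4.60; power = Φ(2.17 − 1.96) = 58%; error = 2 × (1 − Φ(1.96/1.296)) = 13%.

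A simulation of 100,000 trials per ICC gave type I errors of 8.9%, 13.1% and 23.7% for the test that ignores site. It gave site-level powers of 36%, 29%, 25% and 18%.

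**Step 3: can more patients restore 80%?** With two sites per arm, n per arm = 69.2 × (1 − ICC)/(1 − 69.2 × ICC/2). This is about 105 at ICC 0.01 and about 220 at ICC 0.02. The denominator reaches zero at ICC = 2/69.2 = 0.029. From there on no number of patients at these four sites is enough, because the site component of the variance does not shrink with n.

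**The case against.** The strongest reply is that the analysis half rests on silence. The covariate list under Analyses is given as examples, this is a condensed article, and a site term or small-cluster method may stand in an analysis plan or in the appendices, which are not shown. That is right. A reader might infer that the analysis will ignore site and that its intervals will be too narrow; the text does not establish this. The type I figures describe a patient-level test that ignores site, if that is what is run. The reply does not rescue the power statement, which stands in the article as a number. A valid site-level test has 2 df, and putting site type into it leaves 1.

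Four further readings are tempting and too strong:
- *The figure requires sites that do not differ at all.* The arms are matched by site type, so the acute/geriatric difference is balanced and can be adjusted for. Only the remaining variance counts.
- *Every site difference goes wholly into the arm effect.* Differences between the two sites within an arm partly reach the standard error when site is omitted. Only the contrast of arm averages is aliased with treatment.
- *No model can separate site from arm.* Replication within arms does give an estimate of site variance. It is very imprecise, not impossible.
- *The feasibility work shows that CTM scores differ between sites.* It concerns how the intervention was delivered. It gives no ICC and says nothing about scores under standard care. It makes an assumption of zero site variance hard to take for granted, and no more.

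The article is also open about being non-randomised and explains that patient-level randomisation risked contamination. That concedes possible confounding; it does not supply a basis for the power figure.

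**Conclusion.** The point holds for the stated sample size. The 70 per group for 80% power is conditional on no residual between-site variance, and the article does not say so while describing an intervention whose delivery varies by setting. At ICC 0 the patient-level figures of 80% and 5% are correct. At assumed ICCs of 0.01 to 0.05 the power is about 68% to 40%, and the error of a test that ignores site about 9% to 23%.

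These sizes rest on the assumed ICCs and on 35 analysable patients per site. Unequal sites would make them worse. Precision gained from covariates is not counted and would help. Clustering by rehabilitation team is not counted either. Separately, a two-versus-two non-randomised comparison cannot tell the intervention apart from pre-existing differences between these sites, and no ICC correction changes that.

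**What to change.** 1. **Sample size.** State that the 80% power assumes no residual between-site variance in CTM score, and give the power over a range of ICCs, such as 0.01, 0.02 and 0.05.
2. **Primary analysis.** Report the effect with sensitivity intervals whose SE is multiplied by √(1 + (m − 1) × ICC) over that range. With m = 35 the multipliers are √1.34 = 1.16, √1.68 = 1.30 and √2.70 = 1.64. Do not rely on cluster-robust standard errors with four clusters.
3. **Site type.** Adjust for acute versus geriatric, and report the acute-versus-acute and geriatric-versus-geriatric contrasts separately as a consistency check.
4. **Conclusion.** Word it as a difference between these sites, since arm and site remain confounded whatever ICC is used.

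The cost is wording and a few lines of analysis, with no extra patients or sites. The stated power becomes less favourable and the sensitivity intervals are wider. For an observed difference of 10 points, the 95% half-width goes from 1.96 × 3.55 = 7.0 at ICC 0 to 1.96 × 5.83 = 11.4 at ICC 0.05, which would include zero.
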